### Clinician recruitment process

Clinical staff will be informed about the project through education sessions at clinical and multidisciplinary team (MDT) meetings and be given a written invitation to participate. Interested clinicians will be provided with an electronic PISCF to read. Either hard copies of signed consent or scanned electronic versions will be acceptable and collated by the project officer prior to the clinician seeing study patients. All clinicians who were approached to participate consented to the study and reviewed the study questionnaires with the patients.

#### Interventions

The study questionnaires will be repeated at subsequent regularly scheduled follow-up appointments with their clinicians, with a minimum of 2 months between patient completion of questionnaires. Questionnaires will be administered at baseline, with a minimum of two and a maximum of three, follow-up time points. iPads were chosen as the delivery platform because they are portable, have a user-friendly interface, are capable of hosting software that can automatically generate reports and associated documents and are a secure format for data management as they are encrypted by default. All questionnaires used in this study have been validated in previous studies.

At each visit, all patients will be required to complete two short questionnaires that are used to assess their psychosocial distress and quality of life: (1) the National Comprehensive Cancer Network’s Distress Thermometer and Problem List for Patients^19^ and (2) EuroQoL’s EQ-5D-5L (five dimensions, five levels) and Visual Analogue Scale.^20^ Patients who score above the clinical cut-off score on the Distress Thermometer (4 or above) will be triaged to complete an additional three questionnaires: the Melanoma Concerns Questionnaire (MCQ-28),^21^ the Depression, Anxiety and Stress Scale (DASS-21)^22^ and the European Organisation for Research and Treatment of Cancer (EORTC)’s Quality of Life Questionnaire - Cancer (QLQ-C30).^23^ These additional questionnaires will provide more detailed information about potential areas of support needs. Completion time for all five questionnaires is expected to be less than 30 min. All questionnaires are provided in online supplemental appendix 1.

10.1136/bmjopen-2022-066852.supp1Supplementary data

Results from the completed questionnaires will be automatically generated, emailed to the clinic secretary and printed for the treating clinician in real time, so the results can be discussed during their consultation, along with medical concerns. Patients who request a copy of their results (by selecting the appropriate box in the ‘About You’ survey) will receive a summary of their scores by email, prior to their imminent appointment. Participants who score 3 or above on any of the five domains covered in the EQ-5D-5L questionnaire^20^ (mobility, self-care, usual activities, pain/discomfort and anxiety/depression) may require clinical intervention (3=moderate, 4=severe, 5=extreme limitations). There are no melanoma-specific cut-off scores indicating the need for clinical intervention, for the QoL questionnaires MCQ-28^21^ and EORTC QLQ-C30.^23^ Changes in scores for these two questionnaires will be recorded at each time point, allowing for manual inspection of changes over time. A deterioration in EORTC QLQ-C30 scores of 10 points or more between visits is commonly regarded as clinically significant.^24 25^ Recommendations and referrals for additional support services will be based on the questionnaire scores and clinical experience of the clinicians and be made in collaboration with the patient. Further information on reporting processes is available in online supplemental appendix 2.

10.1136/bmjopen-2022-066852.supp2Supplementary data

After all rounds of patient questionnaires (baseline plus 2–3 follow-up rounds per patient) have been completed, all patients, clinicians and clinic staff involved in the project will be asked to complete an electronic survey providing quantitative and open-ended assessments of their experiences with the PROMs questionnaires. In addition, approximately 20% of patients (10 patients), all study clinicians and clinic staff with major involvement in the study will be invited by the research team to participate in a short (10 min) confidential interview to expand on their survey responses. Patients will be purposively sampled to maximise response variation, based on a range of individual views and experiences as identified from their survey results. Patients who complete an interview will be offered a US$30 gift card to thank them for their time, while clinicians and clinic staff who participate in an interview will not be reimbursed. Figure 1 provides a study flow chart from the patient’s perspective and figure 2 provides the study overview from the clinician’s perspective.

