### Study design and setting

ePROMs-MELanoma is a prospective, longitudinal intervention study incorporating mixed methods (quantitative surveys and qualitative interviews). Although there is no control group, the design incorporates before-and-after study design elements allowing for comparisons of psychosocial health and quality of life in individuals with stage III melanoma before and after the introduction of ePROMs. This study will be conducted at surgical and medical melanoma clinics at MIA and at Royal Prince Alfred Hospital (RPAH), Sydney, NSW, Australia.

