### Patient perceptions

Patient ratings of feasibility and acceptability will be assessed in several ways. The first is by the proportion of eligible patients approached who completed baseline and at least one set of follow-up PROMs data. If 60% of patients meet this requirement, the study will be deemed feasible and acceptable overall.

Data on individual patient measures of feasibility and acceptability will also be collected. In the first set of two triage questionnaires, all questions are mandatory, but with the second set of three questionnaires, patients are not required to answer all questions. Metadata from the patients who are triaged to complete the second group of questionnaires will be collected to provide an estimate of the mean time taken to complete the PROMs questionnaires and the amount of missing data (providing a second measure of patient acceptability for those who completed all five questionnaires). If patients take more than 30 min to complete the five questionnaires, they will be considered as not having met this acceptability criteria. Additional measures will include changes in baseline and follow-up scores and the proportion of patients who: ‘agree or strongly agree’ that the PROMs were easy to complete and that the questions they completed measured issues they considered important to their QoL (online supplemental appendix 3a). Semistructured interviews with patients will also assess feasibility and acceptability through the following main question themes: enjoyment of completing the PROMs; changes in patient–clinician communication; changes in their management; and improvements or challenges they found in the processes.

10.1136/bmjopen-2022-066852.supp3Supplementary data

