### Secondary outcomes

Research and clinical psychologists at MIA will use identified unmet needs from this study to inform future research into the development of support programmes at MIA. The extent to which the routine use of PROMs in clinical practice can improve patients’ emotional and physical problems will be assessed through changes in referral rates, referral uptake rates and patients’ QoL scores over time. Patient and clinician interviews will allow for more extensive evaluation of this aspect of the study.

The utility of this framework for the data systems required to enable electronic data capture and feedback to clinicians will be assessed in patient, clinician and clinic staff surveys and interviews as well as assessment by the project team. End-of-study surveys will highlight the perceived ease of use, usefulness, relevance and importance of ePROMs to each group (online supplemental appendix 3). Data will also be collected on time taken to complete questionnaires and on the number of times the questionnaires were completed (out of a maximum of 3–4 time points). In addition, the number of questions answered in the second set of three questionnaires (all questions in the first set of two questionnaires are mandatory) will be recorded.

All participating clinicians are experienced in treating stage III melanoma patients and will be asked to review resources prepared for this study. These include three short videos about PROMs, referral pathways and the project details and support services referral information on the MIA intranet. The aim of these resources is to help clinicians familiarise themselves with the objectives of the study and the use of PROMs in an oncology setting. Online supplemental appendix 4 contains a list of study investigators. Table 1 provides a timeline of expected outcomes.

10.1136/bmjopen-2022-066852.supp4Supplementary data

**Table 1 T1:** Study interventions and assessments timeline

	Baseline			End of study
Time points*	T0	T1	T2	T3
Enrolment				
Eligibility screen	X			
Informed consent	X			
Recruitment	X			
Interventions				
Baseline Patient Questionnaires	X			
Baseline patient demographic info	X			
Follow-up Patient Questionnaires		X	X	X
Clinician Completion Surveys				X
Patient Completion Surveys				X
Clinician completion interviews				X
Patient completion interviews				X
Clinician referral data				X
Patient referral uptake data				X
Patient change over time (T0–T5)				X
Assessments				
Clinician acceptance				X

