### Data analysis and statistical methods

#### Quantitative analysis

Participant demographics and characteristics will be summarised for all participants using means and SD. In addition, the consent, participation and completion rates will be analysed. Consent will be defined as agreeing to participate in the study and returning a signed consent form; participation, as completing some of the components of the study; and completion, as completing all components of the study. Specifically, the proportion of eligible participants who completed the project tasks will be assessed to determine whether the inclusion of ePROMs are acceptable for patients undergoing follow-up treatment for stage III melanoma. Descriptive statistics will be reported for QoL and other questionnaire domain scores at baseline and follow-up time points. Referral and referral uptake rates will also be calculated. The small sample size of 50 for this pilot study precludes any subgroup analysis. Linear mixed effects modelling will be used to account for repeated measures and differential time points among participants. This is similar to analysis of longitudinal data from a clinical trial where measurements at follow-up time points are missing.^27^

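### MCQ-28, DASS-21 and QLQ-C30 exist only at visits where distress is 4 or above, so change on them cannot be recorded at each time point and, if analysed, would understate improvement when distress falls

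*Protocol article*

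**What the plan says.** All places are in the protocol article.

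- **Interventions, collection.** In a paragraph about each visit, all patients complete the Distress Thermometer and the EQ-5D-5L with its VAS. Then: "Patients who score above the clinical cut-off score on the Distress Thermometer (4 or above) will be triaged to complete an additional three questionnaires". These are MCQ-28, DASS-21 and QLQ-C30. The abstract gives the same rule.
- **Interventions, use of MCQ-28 and QLQ-C30.** "Changes in scores for these two questionnaires will be recorded at each time point, allowing for manual inspection of changes over time". The next sentence adds: "A deterioration in EORTC QLQ-C30 scores of 10 points or more between visits is commonly regarded as clinically significant".
- **Patient perceptions.** "Additional measures will include changes in baseline and follow-up scores".
- **Secondary outcomes.** Whether routine PROMs improve patients' problems "will be assessed through changes in referral rates, referral uptake rates and patients’ QoL scores over time".
- **Study design and setting.** The before-and-after elements are described as "allowing for comparisons of psychosocial health and quality of life in individuals with stage III melanoma before and after the introduction of ePROMs".
- **Quantitative analysis.** "Descriptive statistics will be reported for QoL and other questionnaire domain scores at baseline and follow-up time points". A linear mixed model follows, with the remark: "This is similar to analysis of longitudinal data from a clinical trial where measurements at follow-up time points are missing".

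**The concern.** Whether a detailed score exists depends on how distressed the patient is on the day. This has two consequences.

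For the individual, change between two visits is defined only if the Distress Thermometer is at 4 or above at both. Patients who recover drop out of view. Patients who become distressed have nothing to be compared with, although they are the ones a deterioration threshold is meant to find.

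For the group, the scores observed at follow-up come from patients who are still, or newly, distressed. A mixed model handles missing follow-up well when absence can be explained by values already in the model. Here it is explained by the current Distress Thermometer score, which is correlated with the unseen score and is not said to be in the model. The analogy with ordinary missing follow-up therefore does not carry over to these three questionnaires.

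At stake is a secondary conclusion: a real improvement could be reported as small.

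**Working it through.** **Inputs from the article.** 50 patients and 30% with distress needing intervention (Eligibility criteria and sample size); baseline plus two or three follow-ups (Interventions). The article expects approximately 17 triaged patients; 50 × 0.30 = 15, so the figure is reproduced to within 2 patients. I use 15.

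**Assumptions, not in the article.** Distress and the detailed score are treated as standard normal, both scaled so that lower is better. The same-visit correlation ρ and the between-visit correlation r each range over 0.4 to 0.8. Where distress falls, it falls by 0.50 SD.

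**Cut-off.** c = z(0.70) = 0.524. With λ(x) = φ(x)/(1 − Φ(x)), λ(c) = 1.159 and λ(c + 0.5) = 1.545.

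**1. Who has no pair of scores.** The share of baseline-triaged patients without a score at the next visit is 1 − P(at or above c at both)/0.30, from the bivariate normal distribution with correlation r.

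| r | Distress falls 0.50 SD | No shift in distress |
|---|---|---|
| 0.4 | 73% (10.9 of 15) | 53% (7.9 of 15) |
| 0.6 | 65% (9.8 of 15) | 42% (6.4 of 15) |
| 0.8 | 57% (8.5 of 15) | 30% (4.4 of 15) |

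Patients at 4 or above for the first time at that visit, and so without an earlier score, number 1.2 to 3.5 of 50 if distress falls and 4.4 to 7.9 of 50 if it does not. The gap in individual change scores is there either way.

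**2. Difference in observed means, true improvement 0.50 SD in both.** Observed change = −0.50 + ρ × (1.545 − 1.159).

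- ρ = 0.4: −0.346, so 31% of the improvement is hidden
- ρ = 0.6: −0.269, 46% hidden
- ρ = 0.8: −0.191, 62% hidden

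Simulated means scatter slightly more widely, 0.17 to 0.37 SD.

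**3. Random-intercept mixed model of the gated score alone, same truth.** Simulated over three visits, the model shows an improvement of 0.20 SD (ρ = 0.8, r = 0.4) to 0.41 SD (ρ = 0.4, r = 0.8), and about 0.32 SD at 0.6/0.6. About 18 to 60% is hidden. The model helps a little but does not remove the selection.

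**4. No mean shift in distress.** The two λ terms are then equal and cancel in step 2. In simulation the mixed model gives −0.48 to −0.51 against a true −0.50, and about 0 (0.00 to 0.01) against a true 0.

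**5. Distress Thermometer added to the model.** Change = time coefficient + Distress Thermometer coefficient × mean Distress Thermometer change in all patients. With the truth of step 3, this returns −0.48 to −0.51 against −0.50. It works because the simulated relation is linear; below the cut-off no detailed score is ever observed to test that.

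**The case against.** The strongest reply is that the article never says the gated questionnaires supply the before-and-after result. Study design and setting and Secondary outcomes do not name them, and Interventions describes the two universal questionnaires as the ones that assess psychosocial distress and quality of life. This stands. A reader might infer that the whole before-and-after comparison is biased. The text does not support that, because the quality-of-life change may be meant as EQ-5D-5L. It does not settle the matter the other way either: Interventions also calls MCQ-28 and QLQ-C30 quality-of-life questionnaires, and Quantitative analysis covers quality-of-life and other questionnaire domain scores without distinction.

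Second, the sentences on recorded change and the 10-point figure sit in a passage on clinical management, and the 10 points are a literature convention rather than an endpoint. Also fair: a clinician facing a newly distressed patient still has that day's full set of scores, and referral rests on scores plus judgement. The stated comparison remains unavailable for that patient.

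Third, which outcomes and covariates enter the mixed model is commonly left to an analysis plan. Silence on that is not the point here. The point is that the article offers an analogy with ordinary missing follow-up that does not fit scores withheld by rule.

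Fourth, the group-level bias depends on mean distress moving, as step 4 shows.

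A reader might also infer that triage happens once and the set is then repeated, so that regression to the mean would produce a false improvement. That runs against the each-visit wording in Interventions, and the flow charts that might settle it are not shown. I do not rest anything on it.

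**Conclusion.** The point holds in a limited form. As written, change in MCQ-28 and QLQ-C30 cannot be recorded at each time point for patients who fall below 4 or newly reach it, and DASS-21 follows the same rule. That much needs no assumption beyond reading the gate as applying at each visit.

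The bias is conditional on two things: that the planned change in quality-of-life scores includes these questionnaires, and that mean distress falls. If both hold, roughly 20 to 65% of a 0.50 SD improvement is hidden, under normality and correlations of 0.4 to 0.8 that the article does not give. Without a shift in distress there is little or no group-level bias, though individual pairs are still missing.

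Change on the Distress Thermometer, EQ-5D-5L and VAS is not affected, nor are the 60% criterion, referral data and interviews. This is a secondary matter in an uncontrolled feasibility pilot, but worth correcting because the correction is cheap.

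**What to change.** Keep the gate; it limits questionnaire burden, as the article intends.

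1. In Secondary outcomes and Quantitative analysis, name the Distress Thermometer, EQ-5D-5L and VAS as the measures for the before-and-after change. All patients already complete them at each visit.
2. Report MCQ-28, DASS-21 and QLQ-C30 at each visit, with n, as a description of patients distressed at that visit.
3. Treat any change estimate on these three as exploratory, and take it only from a model that includes the Distress Thermometer score recorded at every visit. State that it relies on a linear relation below the cut-off. Ruling out every such model would be stricter than needed.
4. In Interventions, limit the 10-point QLQ-C30 comparison to patients with a score at both visits.

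The cost is wording only, with no added burden, and it can be done with 36 patients already recruited. The downside is that no main claim of change can be made from the three detailed questionnaires.

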**Figure 1 F1:**
[figure not shown]
Patient’s perspective.

**Figure 2 F2:**
[figure not shown]
Clinician’s perspective.

### Outcomes

The primary intended outcome of this study is to determine whether completion of PROMs electronically are considered by both patients, clinicians and clinic staff as feasible and acceptable when incorporated into routine clinical care. Secondary outcomes include assessment of whether these measures help identify people who need and would benefit from further support/referral; the production of a framework for the data systems required to enable electronic data capture and feedback to clinicians, useful in many other applications and clinical specialties; and the utility of clinician training resources. The primary outcome has three components.

### Patient perceptions

Patient ratings of feasibility and acceptability will be assessed in several ways. The first is by the proportion of eligible patients approached who completed baseline and at least one set of follow-up PROMs data. If 60% of patients meet this requirement, the study will be deemed feasible and acceptable overall.

Data on individual patient measures of feasibility and acceptability will also be collected. In the first set of two triage questionnaires, all questions are mandatory, but with the second set of three questionnaires, patients are not required to answer all questions. Metadata from the patients who are triaged to complete the second group of questionnaires will be collected to provide an estimate of the mean time taken to complete the PROMs questionnaires and the amount of missing data (providing a second measure of patient acceptability for those who completed all five questionnaires). If patients take more than 30 min to complete the five questionnaires, they will be considered as not having met this acceptability criteria. Additional measures will include changes in baseline and follow-up scores and the proportion of patients who: ‘agree or strongly agree’ that the PROMs were easy to complete and that the questions they completed measured issues they considered important to their QoL (online supplemental appendix 3a). Semistructured interviews with patients will also assess feasibility and acceptability through the following main question themes: enjoyment of completing the PROMs; changes in patient–clinician communication; changes in their management; and improvements or challenges they found in the processes.

10.1136/bmjopen-2022-066852.supp3Supplementary data

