By including the collection and evaluation of ePROMs data into the routine care for patients with stage III melanoma, the treating clinician will be able to identify patients who are experiencing deterioration in quality of life or psychological distress. Once identified, these patients may then be referred to the appropriate allied health professionals (eg, psychologist, specialist nurse, physiotherapist, occupational therapist and social worker) for appropriate support.

The primary aim of this pilot study is to evaluate the feasibility and acceptability of implementing ePROMs into routine care from the perspectives of both stage III melanoma patients and their treating clinical team (ie, surgeons, dermatologists, medical oncologists, psychologists and melanoma nurses). If the pilot results demonstrate technical, administrative and logistical feasibility, as well as patient, clinician and financial acceptability, this pilot will be expanded to all melanoma clinics within Melanoma Institute Australia (MIA). This expansion will provide an opportunity to collect and analyse a greater volume of data and to potentially serve as a model for wider roll-out of ePROMs across the public and private healthcare sectors in NSW and other states and territories of Australia.

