### Clinician perceptions

It is also important to assess the feasibility and acceptability of this project from the clinicians’ perspective. Measures include whether they found the PROMs data provided to them to be useful, timely, easy to understand and appropriate for their patient population. Clinicians will be approached to expand on their survey responses (online supplemental appendix 3b) in a semistructured interview. The key themes to address are related specifically to the PROMs instruments and the information generated for the clinician; changes in patient management; improvements in patient–clinician communication; and any key challenges or improvements that they can identify regarding the processes.

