### Clinic staff perceptions

Clinic staff including clinical nurse consultants and medical secretaries will also be asked to assess the feasibility and acceptability of incorporating QoL questionnaires into their clinic’s routine practice (online supplemental appendix 3c). If they consider the additional workload or clinic disruption to be unacceptable or burdensome, then this will have a major impact on the feasibility assessment of continuing this practice once the pilot study has been completed.

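### The 60% completion rule decides the overall feasibility and acceptability verdict on patient completion alone, although the primary outcome has patient, clinician and clinic-staff components

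*Protocol article*

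**What the plan says.** The Outcomes section of the protocol article defines the primary outcome as whether electronic PROMs are "considered by both patients, clinicians and clinic staff as feasible and acceptable when incorporated into routine clinical care", and adds: "The primary outcome has three components". Three subsections follow, for patients, clinicians and clinic staff.

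The patient subsection announces several measures. The first is "the proportion of eligible patients approached who completed baseline and at least one set of follow-up PROMs data", and the rule attached to it is: "If 60% of patients meet this requirement, the study will be deemed feasible and acceptable overall". The same subsection then lists further patient measures: missing data, a completion-time criterion ("If patients take more than 30 min to complete the five questionnaires, they will be considered as not having met this acceptability criteria"), and patients' agreement that the questionnaires were easy and covered what matters to them.

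The clinician subsection opens: "It is also important to assess the feasibility and acceptability of this project from the clinicians’ perspective". The clinic-staff subsection says that if staff find the workload or disruption unacceptable, "then this will have a major impact on the feasibility assessment of continuing this practice once the pilot study has been completed".

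Two other places bear on the overall judgement. The Introduction sets the condition for expansion: "If the pilot results demonstrate technical, administrative and logistical feasibility, as well as patient, clinician and financial acceptability, this pilot will be expanded". The Secondary outcomes section says that overall project success will be judged with a published implementation-research framework. Table 2 lists its further outcomes, including appropriateness (clinician and staff surveys and interviews) and costs to patients, clinicians and staff.

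**The concern.** The 60% sentence has the study as its subject and an overall verdict as its result, yet its only input is patient questionnaire completion. It is the only numerical criterion in the article attached to an overall verdict, so an analyst looking for the success rule would apply it. Clinician and staff results could not change the outcome, and neither could patients' own ratings of ease and relevance.

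At stake is the answer to the primary question. The study could report that it was feasible and acceptable overall when one or two of its three primary components had failed.

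**Working it through.** The 60% is a chosen cut-off. No formula in the article produces it, so there is no stated figure to reproduce. The check sets the statements side by side and then works out what the literal rule allows.

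**1. What each statement makes the verdict depend on**

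| Place in the protocol article | Decision | Depends on |
|---|---|---|
| Patient perceptions, 60% rule | Overall feasibility and acceptability | Patient completion only |
| Outcomes | Primary outcome | Patients, clinicians, clinic staff |
| Patient perceptions, remaining text | Patient feasibility and acceptability | Completion plus missing data, time, ease, importance, interviews |
| Clinic staff perceptions | Feasibility of continuing the practice | Staff workload and disruption |
| Secondary outcomes and Table 2 | Overall project success | Intervention and implementation outcomes, including clinicians, staff and costs |
| Introduction | Expansion | Feasibility plus patient, clinician and financial acceptability |

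The first row cannot hold together with rows two to five. A verdict that completion alone settles cannot also depend on clinicians, staff or the other patient measures. The last row concerns a different decision, so it does not contradict the first. The article does not say how the 60% rule combines with the other components.

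**2. What the literal rule allows**

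Inputs: threshold 60% (Patient perceptions); at least 50 patients and at least five clinicians (Eligibility criteria and sample size).

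Assume that everyone approached enrols, so the denominator is 50. Completers needed = 0.60 × 50 = 30. With 30 completers the rule is met whether 0 or 5 of five clinicians find the system acceptable, and whatever staff report.

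**3. Precision, with the correct denominator**

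The denominator is eligible patients approached, and the article does not give that number. For x completers out of n, the exact (Clopper–Pearson) 95% limits are the 2.5% quantile of Beta(x, n − x + 1) and the 97.5% quantile of Beta(x + 1, n − x). With 50 enrolled and an assumed consent rate:

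| Assumed consent | Approached n | Completers needed x | Exact 95% CI for x/n |
|---|---|---|---|
| 100% | 50 | 30 | 45% to 74% |
| 80% | 50/0.8, rounded up = 63 | 38 | 47% to 72% |
| 70% | 50/0.7, rounded up = 72 | 44 | 49% to 72% |

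The table stops at 70% because, with exactly 50 enrolled, 60% consent would mean 84 approached and 51 completers needed, more than were enrolled.

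At n = 50 the chance of reaching 30 completers, P(X ≥ 30) for a binomial count, is 0.10, 0.56 and 0.95 at true completion rates of 50%, 60% and 70%. These figures describe the completion criterion. The contradiction in step 1 does not depend on them.

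**The case against.** The strongest defence is context. The sentence stands under a heading about patients, follows a statement that patient ratings will be assessed in several ways, and precedes a paragraph on individual patient measures. On that view, overall means the aggregate patient result, and the next two subsections add the clinician and staff components. This reading is possible, but the sentence does not say it. It would not cure the problem either: completion would still settle patient acceptability whatever the time criterion and the ease and importance ratings showed, although the section calls completion only the first of its measures.

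Three further objections stand, and they limit the point.

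- A reader might infer that reaching 60% triggers expansion. The documents do not support this. The rule does not mention expansion, and the Introduction's condition is conjunctive, so 60% completion with clinicians opposed would not satisfy it.
- A reader might infer that clinicians, staff and costs carry no weight anywhere in the plan, or that the rule displaces the financial condition. Neither follows. The framework around Table 2 covers all three, and financial acceptability is a condition for expansion, not one of the three primary components.
- A reader might count the lack of a confidence interval as a defect. A condensed article may leave that to the statistical analysis plan, so it is not one here.

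**Conclusion.** The point holds as an internal contradiction in the rule for the primary outcome. Taken literally, the rule yields a verdict of feasible and acceptable overall from one patient measure. That conflicts with the three-component primary outcome, the clinic-staff statement, the remaining patient measures and the framework-based assessment of overall success.

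The size is best put as what the rule permits: at a denominator of 50, 30 completers pass with any clinician or staff result. This rests on the literal wording and on everyone approached enrolling. With a larger denominator the count changes and the contradiction does not. The harm is confined to a wrong overall verdict, because the expansion decision has its own conditions.

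**What to change.** Reword the sentence in Patient perceptions so that reaching 60% means only that the patient-completion criterion is met. Then state that the study is deemed feasible and acceptable overall only when all three components are judged met: patient (including the other measures in that section), clinician and clinic staff. Because the article sets no threshold for the clinician or staff component, also say beforehand how each will be judged. Leave the Introduction's conditions, including financial acceptability, to govern expansion. If the completion proportion is reported with an interval, use eligible patients approached as the denominator.

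This is a wording change that needs no new patients, data or procedures. Its cost is that the overall verdict becomes harder to reach. It should be made before the results are interpreted.
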